### Follow up

2.10

After finishing the treatment of four weeks, follow-up will be done on all patients for three months. Because of the specificity of stroke patients’ recovery, they may accept other rehabilitation treatments during this period. Considering the ethical issue, we will not intervene in this except for the prohibition of additional intradermal needle. We have created rehabilitation diaries and telephone interview forms (TIFs). We will train and ask each patient to record their condition every day after hospital discharge, such as medication used, method and frequency of treatment, AEs, and so on. At the end of each month, our assessors will call patients to enquire their conditions based on the TIFs. At the end of follow-up, participants will be referred for RSSCAN gait system and clinical scales as before. All forms will be collected by the data collectors regardless whether they have withdrawn from the trial assessments for reviewing at the end of this trial.

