### Randomization and allocation concealment

2.8

All participants will be assigned to experimental group or control group in a 1:1 ratio according to a computer-generated randomization list by an independent researcher. In accordance with best practice recommendations for randomized controlled trials, allocation concealment will be employed. Assignments will be sealed in opaque envelopes by a nurse who will be trained before the trial and will not participate in treatment. As only the therapist who opens the envelopes will assign patients to a different group. It is impossible to predict and interference the assignments factitiously. The participants will be blinded. They will be told that they have been randomly allocated to one group, and be treated with regular rehabilitation therapies. Moreover, the outcome assessors and data statistical analysts will remain blinded to the intervention methods. Unblinding will be considered when adverse events (AEs) occur.

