### Outcome measures

2.11

The participations will be examined at baseline, reexamined after 4-week treatment, and again at the end of 3 months’ follow-up. Data will be assessed by trained, certified assessors.

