### Data management and monitoring

2.16

Before the study, we have set up Data Management and Monitoring Committee (DMC) and trained all researchers about data management. DMC is independent from trial investigators, and has no competing interests. First, all assessors will be responsible for the assessment and acquisition of participants’ information during the study. After they finish the Case Report Forms and TIFs completely, 2 data collectors will convert these and rehabilitation dairies to electronic data. All these original data related to the research including paper forms and electronic documents will be archived securely in the Clinical Research Center of Dongzhimen Hospital. Only researchers in our study team will have access to the final complete data, others who have any questions will be required written requests to our data manager to be permitted.

Monitoring is another role and responsibility of DMC. Members of DMC will monitor the overall quality and completeness of the data, examine original documents, interview assessors, and confirm that the study is complied with the principles of this protocol. The monitors will verify that all AEs be recorded in the correct format.

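### The assessors who must stay blinded also make the monthly follow-up calls, an avoidable route for allocation to reach those who rate the 3-month clinical scales

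*Protocol article*

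**What the plan says.** Four places in the protocol article bear on this.

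- Section 2.8 (Randomization and allocation concealment) fixes the blinding: "the outcome assessors and data statistical analysts will remain blinded to the intervention methods".
- Section 2.10 (Follow up) describes the three months after treatment. Patients keep a daily record of their condition, "such as medication used, method and frequency of treatment, AEs, and so on". The next sentence assigns the monthly calls: "our assessors will call patients to enquire their conditions based on the TIFs". The gait test and the clinical scales are repeated when follow-up ends.
- Section 2.11 (Outcome measures) gives the rating to the same role: "Data will be assessed by trained, certified assessors".
- Section 2.16 (Data management and monitoring) joins the duties: "all assessors will be responsible for the assessment and acquisition of participants’ information during the study". Data entry follows: "After they finish the Case Report Forms and TIFs completely", "2 data collectors will convert these and rehabilitation dairies to electronic data".

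The Discussion (section 3) lists as a limitation that some patients given real needles will probably realise which group they are in.

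**The concern.** Blinding of the raters protects the scale scores only if what patients know or suspect does not reach them. Here the plan has the raters telephone every patient, month by month, about how they are, and then score that patient on scales that the Background and the Discussion describe as depending partly on the evaluator. A patient who has guessed the arm, or who mentions a skin reaction or a pricking sensation, could reveal the allocation in such a call. The real device enters the skin and the sham does not (sections 2.9.1 and 2.9.2), so remarks of that kind carry information. Section 2.8 also links AEs to allocation, since it makes their occurrence a reason to consider unblinding.

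At stake is detection bias in the 3-month comparison of the secondary scales listed in section 2.14. The plan would then claim a degree of assessor blinding that its own procedure weakens.

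**Working it through.** No formula applies to a conflict of roles, so the check sets the sections side by side. The only arithmetic is the number of calls.

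1. **Who must be blind?** The outcome assessors (2.8).
2. **Who rates the outcomes?** Assessors (2.11).
3. **Who telephones?** Assessors, monthly (2.10).
4. **Who completes the TIFs?** Section 2.16 names all assessors as responsible for both assessment and gathering information, and has them finish both sets of forms. Nothing separates callers from raters.
5. **What do the calls cover?** Patients' conditions, according to the TIF. The TIF items are not shown. The list of medication, treatments and AEs belongs to the diary, in the preceding sentence. That the calls touch the same matters is a close inference from the word used for both, not a statement in the text.
6. **Is there something to leak?** Yes, for some patients: section 3 concedes it. The safeguards named there (needle-naive patients, kept apart during treatment) protect the patient's blinding. None governs what a patient tells an assessor.
7. **Which ratings come after the calls?** The baseline and 4-week ratings precede every call. Calls fall at the end of months 1, 2 and 3 of follow-up, and the last rating is at the end of month 3. The first two calls clearly precede it; the order of the third call and the final visit is not stated.
8. **Which outcomes are exposed?** The clinical scales of section 2.14, so far as they are scored by a rater; the article does not say how each is administered. The primary gait measures come from a pressure plate run by one trained operator (2.13), and nothing says that this operator makes calls.
9. **How many calls?** Section 2.3 plans 40 patients and inflates for 20% drop-out: 40 / (1 − 0.20) = 50, or 25 per group, which reproduces the stated target. Three calls each give 3 × 50 = 150 at most. For the 40 expected to complete, the number is 3 × 40 = 120. These are counts of contacts, not of expected unblindings.

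**The case against.** The best case for the plan has four parts.

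- **The TIF may be harmless.** Its items are not shown, and a journal article may leave call wording to the full protocol. This stands as a limit on what can be asserted. It does not remove the assignment of duties, which the article itself makes.
- **The calls come late.** Needling has ended, further intradermal needling is prohibited, and other rehabilitation is open to both arms. Answers about current treatment therefore do not reveal the arm, and needle-related AEs belong mainly to the treatment weeks. This stands: a leak needs a patient who knows or guesses the arm, or an AE that points to it.
- **Raters meet patients anyway.** A patient who knows the arm can say so at the 4-week or 3-month visit, whoever telephones. This also stands. The calls add to an existing route, and only that addition is removable by reassigning them.
- **Patient blinding is reasonably built.** The sham looks alike on the surface, is applied at the same points for the same time, and a test of blinding is planned (2.18). That lowers the risk, but a test measures a leak and does not prevent one.

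Three stronger readings are tempting, and the documents do not support them. A reader might infer that the calls do unblind the raters; the text shows only that they could. A reader might extend the problem to the primary outcome, because the step to be analysed is selected by hand; no section ties that selection to the callers. A reader might also attach a size. If 10% to 40% of patients in one arm revealed their allocation and their ratings shifted by 0.3 to 0.5 SD, the bias would be 0.1 × 0.3 = 0.03 SD to 0.4 × 0.5 = 0.20 SD. A two-sided 5% t test with 25 per arm would then reject falsely in about 5.1% to 10.7% of trials. Both inputs are invented, the range runs from negligible to a doubling, and it counts all unblinding, not the part due to the calls.

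**Conclusion.** The point holds in a limited form. The plan promises blinded assessors and then gives that same role the monthly calls and the TIFs, without separating callers from raters. This creates an avoidable route for allocation to reach the people who score the 3-month secondary scales. It is a weakness in a stated assignment of duties, not a proven breach of blinding.

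The conclusion rests on two assumptions: that the calls touch on treatments or AEs, or at least let the patient talk freely about them, and that the callers are the same individuals as the raters, as section 2.16 indicates. Neither the size nor the direction of any bias can be derived from the document. The correction is worth making because it is cheap and because this pilot is meant to lay the ground for a larger trial.

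**What to change.** Amend sections 2.10 and 2.16 in three respects.

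1. Assign the monthly calls and the TIFs to existing staff who do not rate outcomes. The two data collectors in section 2.16 are obvious candidates.
2. State that raters do not see TIF, diary or AE content until the 3-month ratings are complete. No section has the assessors reading the diaries now, so for diaries this only makes the rule explicit.
3. Ask patients not to discuss needling with the raters. This also helps at the face-to-face visits, which reassigning the calls cannot protect.

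If separate callers are in fact already used, a sentence saying so would settle the first item. The cost is a few sentences and extra telephone work for the staff concerned, at most about 150 short calls. Design, sample size and treatment are unchanged. Calls already made by raters cannot be undone, as enrolment is under way (section 3.1), so the report should state from what date the change applied.

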### Outcome measures

2.11

The participations will be examined at baseline, reexamined after 4-week treatment, and again at the end of 3 months’ follow-up. Data will be assessed by trained, certified assessors.

### Basic characteristic variables

2.12

We will conduct demographic information of all the participants at baseline assessments, including sex, age, time from the onset of stroke, medical history, clinical syndrome (left or right hemiplegia), diseased location, and other detailed information. Vital signs such as the resting blood pressure, pulse, respiration rate, and body temperature will be measured every day by nurses.

### Primary outcome measurement

2.13

In the prospective trial, the primary outcome will be the ability of walking, measured by the data from RSSCAN gait system (2 × 0.4m, Olen, made in Belgium). It is a dynamic plantar pressure system, including a walking plate with more than 16,000 sensors distributed, a Footscan 3D box and other supporting software. It is sensitive in detecting parameters when people stand or walk on the sensor array plate. In our study, we will collect static and dynamic foot-parameters of dynamic plantar pressure distribution, step length, and stride as primary outcome. Plantar pressure distribution includes the peek pressure (PP) in 10 regions of foot: hallux, toes 2 to 5, first to fifth metatarsals, midfoot, medial heel, and lateral heel. PP is the most relied and common used upon plantar pressure parameter.^[31]^ We will observe PP of these 10 regions and the changes after treatment. Step length and stride can reflect the self-selected walking distance.^[32]^ A cross-sectional study indicated that step length symmetry demonstrated a systematic linear trend toward greater asymmetry in groups in the later stages of post-stroke.^[33]^ So we will measure these indexes to evaluate intervention as well.

According to the manufacturer's manual, the RSSCAN gait system will be calibrated before each individual's test. Patients’ weight and foot size will be recorded into computer for calibration. Patients will be instructed to get familiar with the walking plate every time before the testing. They will be told to walk at their comfortable pace and look straight ahead. A walking phase to be considered as reliable when meets the following criteria: at least 1 complete footprint for each foot, a heel-strike pattern, no obvious adjustment in gait pattern to contact the plate. We will select the most representative step of each foot to analysis. All tests will be done by the same RSSCAN system operator, who has received standardized training before.

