In previous work, patients’ motor function and life ability were assessed by scales, which lacks objectivity because the score depends on the researchers partly. Very few studies focused on the objective measure of evaluation.^[13–15]^ The clinical intervention strategies which are used must be backed by a high level of assessment-based support. The RSSCAN gait system can provide biomechanical parameters such as dynamic plantar pressure distribution, step length, foot impulse curve, walking support phase, pace, stride frequency, among others.^[16]^ Because it is a reliable means for foot-examination quantitatively and automatically, it had been used to detect the gait parameters for distinguishing between normal and pathological gait,^[17]^ classifying foot types,^[18]^ even assessing the effect of foot surgery.^[19]^ We mainly use the RSSCAN gait system to evaluate the motor function of lower limb in the present work.

Based on the above, we conceived this clinical pilot trial with the following primary aims. First is to collect preliminary data to observe whether intradermal needle add-on therapy leads to a more effective recovery for patients with post-stroke hemiplegia. Second is to adopt objective outcome measures to elucidate the biomechanical mechanisms underlying the effects.

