In clinical studies, evaluations play an important role. A majority of previous studies adopt clinical rating scales to estimate the therapeutic effect, which have been proven to be prone to some errors associated to the evaluators’ subjective perception.^[39]^ Lack of objective assessments affects the quality of results.^[40]^ To overcome this limitation, this study may potentially confirm whether or not intradermal needle is effective for post-stroke hemiplegia by using biomechanical outcome measurements from the RSSCAN gait system. It can provide objective kinematic data of static and dynamic gait. Vertical plantar pressure dispersion of the foot will be recorded, processed, and graphically displayed in terms of sequential gait changes.^[41]^ It helps to remove some of the unavoidable guess work from essential diagnostic and therapeutic procedures. Our previous work has shown that it is affordable, accurate, and reliable for the assessment of motor function in patients with stroke.^[42]^

The unavoidable limitations of our trial consist of three domains. First, despite the assessor-blinding, some patients who got treated with intradermal needles will likely know which group they are in. Therefore, we will select participants who have never used these needles and keep participants separate from each other during the treatment procedure. Next, after completion of the 4-week treatment, a 3-month follow-up will be conducted. This time span means that participants’ compliance could be a problem. Thus, we designed a recover diary and regular telephone follow-up to minimize this situation. The last limitation is the small sample size, as this trial was proposed to be a pilot study for further larger scaled clinical study.

This study focuses on the biomechanical effect of intradermal needle embedding for post-stroke hemiplegia, so far there is no study of this aspect. If the trial is successfully carried out, we may provide feasibility data and basic information for utilizing this therapy and build a stronger foundation for other studies.

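### The primary gait outcome is taken from one step per foot, picked by an undefined criterion, which makes it hard to reproduce and noisier than it need be

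*Protocol article*

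**What the plan says.** Section 2.13 of the protocol article names "dynamic plantar pressure distribution, step length, and stride as primary outcome". Plantar pressure means peak pressure in 10 foot regions, so with step length and stride there are about 12 parameters per foot.

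A walk counts as reliable if it shows "at least 1 complete footprint for each foot, a heel-strike pattern, no obvious adjustment in gait pattern to contact the plate". The rule for what enters the analysis follows: "We will select the most representative step of each foot to analysis". The section gives no definition of a representative step, no number of passes and no averaging. It adds: "All tests will be done by the same RSSCAN system operator, who has received standardized training before".

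The reason for using the plate is given elsewhere. The Background faults earlier work based on rating scales, "which lacks objectivity because the score depends on the researchers partly". The Discussion repeats the theme ("Lack of objective assessments affects the quality of results") and says of the gait system: "It helps to remove some of the unavoidable guess work from essential diagnostic and therapeutic procedures".

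Two other places matter. Section 2.8 says "the outcome assessors and data statistical analysts will remain blinded to the intervention methods". Section 2.18 puts both between-group and within-group changes into the main analysis.

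**The concern.** The plate records pressures automatically, but the value analysed depends on which step is kept. If nobody can say in advance which step that is, two competent people could extract different primary outcomes from the same recording. This is the researcher dependence that the protocol criticises in rating scales.

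Keeping one step also throws away information. Steps vary within a visit, and that variation enters both the baseline and the follow-up value, so it counts twice in the change score. With 20 patients per group planned for analysis, avoidable variance is costly. In a pilot meant to inform a larger trial, it would also carry into the variability estimates used for planning.

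This is not a detail left to a fuller document. The article states the rule, and an analysis plan cannot recover steps that were dropped at measurement.

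**Working it through.** **The plan's own figure.** The protocol gives no standard deviation, effect size or power. Its only sample-size arithmetic is 40/(1 − 0.20) = 50 recruited, 25 per group. This reproduces and is not in dispute.

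**Do the validity criteria settle which step is used?** No. They decide whether a walk is acceptable. Selecting one step implies that more than one acceptable step may exist, and nothing ranks them.

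**Does one step per foot suit every primary parameter?** Peak pressure can be read from one footprint. Stride runs between two footprints of the same foot, so a minimum of one complete footprint per foot cannot supply it. Either the selection sentence covers pressure only, or it does not work for stride. The text does not say which.

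**How much precision is lost?** The inputs below are assumptions; none is in the document:
- R, the reliability of a single step: 0.6, 0.7 or 0.9
- true baseline/follow-up correlation: 0.8
- three valid steps per foot per visit
- all unreliability is step-to-step noise

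In units of single-step variance,

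variance of change = 2[R(1 − 0.8) + (1 − R)v],

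where v is the within-patient error variance of the value used, relative to one arbitrary step:
- v = 1 for an arbitrary step.
- v = 1/3 for the mean of three steps.
- v = 0.45 for the step nearest the patient's own mean on a single parameter (simulation). This is the best case for selection.
- v = 0.64 to 0.80 for the one step nearest the patient's mean over 12 parameters jointly (simulation, between-parameter correlation 0.6 down to 0).

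| R | mean of 3 | best case, v = 0.45 | 12 parameters, v = 0.64 | 12 parameters, v = 0.80 | arbitrary, v = 1 |
|---|---|---|---|---|---|
| 0.6 | 0.507 | 0.600 | 0.752 | 0.880 | 1.040 |
| 0.7 | 0.480 | 0.550 | 0.664 | 0.760 | 0.880 |
| 0.9 | 0.427 | 0.450 | 0.488 | 0.520 | 0.560 |

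Example, R = 0.6: the mean gives 2[0.12 + 0.4/3] = 0.507, and v = 0.80 gives 2[0.12 + 0.32] = 0.880. The cut is 1 − 0.507/0.880 = 42%.

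Reduction in the variance of change from averaging:

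| R | against best case | against 12-parameter selection | against arbitrary step |
|---|---|---|---|
| 0.6 | 16% | 33–42% | 51% |
| 0.7 | 13% | 28–37% | 45% |
| 0.9 | 5% | 13–18% | 24% |

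**Sensitivity to the correlation.** With a true correlation of 0.5 the first term becomes R(1 − 0.5). Against an arbitrary step the cuts fall to 38%, 31% and 12% for R = 0.6, 0.7 and 0.9. Example: 1 − 2[0.30 + 0.4/3]/2[0.30 + 0.4] = 1 − 0.867/1.400 = 38%.

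**How much room is there for judgement?** Always taking the most favourable of three steps would shift one parameter by 0.84 within-patient SD. Multiplying by √(1 − R) gives 0.27 total SD at R = 0.9 and 0.53 at R = 0.6. This is a ceiling on what selection could do, not evidence that it happens.

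**The case against.** **A representative step is not a random one.** This stands. A step chosen to be typical carries less noise than an arbitrary one, so the 24–51% range describes a rule that the protocol does not state. But one step must serve about 12 parameters, and a step typical on one need not be typical on the others. The gain shrinks and does not reverse.

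**Some of the noise may not be step-to-step.** This also stands. Day-to-day or session error would not shrink by averaging within a visit. The percentages would then be smaller, as they would with a lower correlation.

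**Blinding protects the comparison.** A reader might infer that the operator picks the step by eye, knows the visit, and so biases the difference between arms. The document does not support this. It does not say who selects or how, and it names the operator only as running the tests. Assessors and analysts are blinded and the control is a sham. The Discussion's concession concerns patients guessing their group, not whoever selects. If the selector is blind to arm, knowledge of the visit should not by itself favour one arm. It would still touch the within-group changes that section 2.18 includes in the main analysis, and no blinding to visit is stated.

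**An article condenses.** A fuller protocol may define the term. Even so, the stated rule keeps one step, and a definition would not restore the discarded ones.

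**The trial is an unpowered pilot.** True, so no stated power target is missed. Reproducibility and usable variance estimates still matter to its stated purpose.

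**Conclusion.** The point holds. The primary outcome rests on one step per foot, chosen by an undefined criterion. That conflicts with the protocol's own case for an objective measure and wastes data from the same visit.

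What is firm is that the measurement cannot be reproduced from the stated rule and that avoidable noise is added. The noise arises only where more than one valid step is recorded, which the wording implies. Within-group changes are exposed to selection by visit. Between-arm bias is possible but not shown.

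Under the assumptions above, at a correlation of 0.8, averaging three steps would cut the variance of change by about 13–42% against a selected step serving about 12 parameters, and by about 5–16% in the best case for selection. It reaches 24–51% only against an arbitrary step. The direction is the same throughout, but the size cannot be fixed without step-level data.

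**What to change.** Replace the selection sentence in section 2.13 with a fixed rule:
- Record a set number of accepted passes per visit (for example three).
- Analyse the mean or median of all steps that meet the stated validity criteria, for each foot separately.
- Have validity judged by someone blind to group and, where possible, to visit. Some judgement remains in the criterion about gait adjustment, so this blinding should be written down.
- Take stride only from passes that contain two footprints of the same foot.

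Section 3.1 says enrolment is under way. For patients already measured, re-process the stored recordings by the same rule at every visit, so that baseline and follow-up stay comparable. Section 2.16 says original data are archived but not whether unselected passes are kept, so check this first. Where they are missing, use one rule for all of that patient's visits and report how many patients are affected.

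Cost: possibly a few extra passes over a 2 m plate per visit (the current number is not stated), slightly more effort for patients, and some re-processing. No new equipment or patients are needed.
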